### Trial governance

The trial will be overseen by a Trial Steering Committee (TSC). The TSC will have an independent chair and members with clinical expertise. Meetings will be scheduled before enrolment and regular meetings held either by teleconference or face-to-face.

Day-to-day management of the study will be co-ordinated by a central Trial Management Group (TMG) at the Kumasi Centre for Collaborative Research (KCCR) in Tropical Medicine including the Principal Investigator, Senior Trial Clinician and Trial Coordinator and the Trial site Coordinators. This group will provide regular supervision of the trial and ensure that it is conducted in accordance with the principles of GCP and other relevant regulations.

An independent Data Monitoring Committee (DMC) has been established to provide oversight of the study. The DMC will review safety and efficacy data during the active phase of the trial. They will advise on the continued recruitment of trial participants. This committee consists of an independent chair, a statistician and members with clinical and methodological expertise. An independent clinical expert panel (separate from the DMC) has been established to provide external clinical assessment of outcomes where required, for example judging potential paradoxical reactions.

#### Auditing

The study may be subject to audit by the London School of Hygiene & Tropical Medicine (LSHTM) under their remit as sponsor and other regulatory bodies to ensure adherence to GCP.

#### Harms

The study has made provision once any Adverse Events (AEs) and/or Serious Adverse Events (SAEs) are identified. An AE/SAE form will be completed and submitted to the study coordination centre with as much detail of the event that is available at that time. SAEs and Serious Adverse Reactions (SARs) will be reported to the study coordination centre within 24 hours of the local site being made aware of the event. Participants will be offered appropriate treatment within the health facilities and followed up or referred to a higher level of care if required. If awaiting further details, a follow-up SAE report will be submitted promptly upon receipt of the outstanding information. The PI will record the event with an assessment of seriousness, causality and expectedness.

Any events relating to a pre-existing condition or any planned hospitalisations for elective treatment of a pre-existing condition do not need reporting as SAEs.

All SAEs assigned by the principal investigator or delegate as both suspected to be related to treatment with investigational product (IMP) and unexpected will be classified as suspected unexpected serious adverse reactions (SUSARs) and will be subject to expedited reporting to the Regulatory Authority. The Sponsor (or delegate) will inform the relevant bodies of SUSARs within the required expedited reporting timescales.

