#### Criteria for discontinuing or modifying allocated interventions

In the event that a participant becomes pregnant after starting the study medication, she will be withdrawn and followed up by an obstetrician throughout the pregnancy to assess any effect on the pregnancy outcome. If a live baby results, then the baby will be followed up by a paediatrician for two years.

Participants on anti-hypertensive drugs will have their blood pressure closely monitored to allow for appropriate decision-making. As part of the trial team, an experienced physician will be available to make decisions regarding treatment, which may include adjustment to doses of antihypertensives if need be.

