#### Secondary outcomes

The following secondary outcomes will be assessed:
The proportion of participants with no viable MU organisms, as assessed by a combined 16s rRNA reverse transcriptase/IS2404 real-time qPCR assay, detectable at Weeks 2, 4, and 6, during antimicrobial intervention and at Week 8 after both groups have completed rifampicin and clarithromycin treatment.The proportion of participants achieving complete healing of lesions at Week 20, where complete healing is defined as re-epithelialisation of ulcerated area with stable scar formation during a three-month observation period.The proportion of participants with reoccurrence of BU in each treatment arm; indicator of reoccurrence being the appearance of a new lesion within 12 months of treatment and is not considered as a paradoxical reaction. This will be assessed by the presence of viable micro-organisms detected by culture or 16S rRNA assay after completion of antibiotic treatment and complete healing of the initial lesion.The proportion of participants with paradoxical reaction in each arm of intervention. Paradoxical reaction is defined as:
an initial improvement in the clinical appearance of lesion upon antimicrobial treatment of BU followed by deterioration of the lesion or its surrounding tissuesor the appearance of a new lesion(s)or examination of excised tissue from the clinical lesion showing evidence of an intense inflammatory reaction consistent with a paradoxical reaction.
The proportion of participants who experience secondary infection defined as the occurrence of new purulent discharge within the BU lesion accompanied by microbiological evidence of infection by an organism other than MU.

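### The SAE exemption for pre-existing conditions has no exception for worsening, so serious deterioration of the Buruli lesion or of a comorbidity may go unreported as an SAE, in conflict with the SAR and SUSAR rules beside it

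*Protocol article*

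**What the plan says.** Three rules in the Harms section of the protocol article bear on this point.

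- The exemption: "Any events relating to a pre-existing condition or any planned hospitalisations for elective treatment of a pre-existing condition do not need reporting as SAEs".
- The 24-hour duty: "SAEs and Serious Adverse Reactions (SARs) will be reported to the study coordination centre within 24 hours" of the site becoming aware of the event.
- The SUSAR route: "All SAEs assigned by the principal investigator or delegate as both suspected to be related to treatment with investigational product (IMP) and unexpected" are classified as SUSARs and go to expedited regulatory reporting.

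The same section has the principal investigator assess each event for seriousness, causality and expectedness.

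Other parts of the article show what the exemption touches:

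- Eligibility criteria: every participant must have a nodule, plaque or ulcer and a positive PCR for *M. ulcerans*.
- Secondary outcomes: paradoxical reaction is defined partly as an initial improvement "upon antimicrobial treatment of BU followed by deterioration of the lesion" or its surroundings. Secondary infection and recurrence are also outcomes.
- Criteria for discontinuing or modifying allocated interventions: "Participants on anti-hypertensive drugs will have their blood pressure closely monitored to allow for appropriate decision-making". A trial physician takes treatment decisions, "which may include adjustment to doses of antihypertensives if need be".
- Trial governance: "The DMC will review safety and efficacy data during the active phase of the trial". A separate expert panel exists "to provide external clinical assessment of outcomes where required, for example judging potential paradoxical reactions".
- Table 1: adverse events and lesion measurements are collected at every follow-up visit and at a treatment-failure visit.

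**The concern.** An exemption of this kind normally keeps routine care of stable, known illness out of the SAE database. This one goes further. Its opening part covers any event related to a pre-existing condition, however serious, unplanned or new in severity. The disease under study was present before enrolment in everyone, so the wording reaches the condition on which the two regimens are most likely to differ.

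The intervention arm receives rifampicin at 20 mg/kg for four weeks and the control arm 10 mg/kg for eight weeks. That is twice the daily dose (20/10 = 2) for half the duration (4/8 = 0.5). The Introduction says that policy makers need evidence on safety. If serious lesion deterioration or serious worsening of a comorbidity is reported as an SAE at one site and left out at another, the SAE comparison between arms is hard to interpret. Participants and the staff who give the drugs know the allocation, so the judgement that an event relates to a pre-existing condition could also be made differently by arm.

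**Working it through.** No arithmetic decides this point. It is settled by setting the rules side by side.

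1. **Scope of the exemption.** The sentence has two parts joined by *or*. The qualifiers *planned* and *elective* belong only to the second part and do not narrow the first. The first part has no condition on severity, on change since baseline or on suspected relation to trial drug.

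2. **Does it reach the Buruli lesion?** The lesion and the positive PCR are entry criteria, so both precede randomisation in every participant (112 planned, Sample size section). The article neither defines a pre-existing condition nor excludes the disease under study. On ordinary wording the lesion is covered.

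3. **Does it reach comorbidities?** Yes, in the same way. Participants already taking antihypertensives are one group for whom the article provides monitoring and possible adjustment during the trial. Serious worsening of their hypertension would fall under the exemption.

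4. **Are such events foreseeable?** The outcome definitions include lesion deterioration on treatment and secondary infection, and Table 1 has a treatment-failure column. Some of these events could meet a seriousness criterion, for example through an unplanned admission.

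5. **Exemption against the 24-hour duty.** The duty names SAEs and SARs; the exemption names only SAEs. A serious lesion event suspected to be drug-related is therefore reportable within 24 hours as an SAR but exempt as an SAE. The article does not say which rule governs.

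6. **Exemption against the SUSAR route.** SUSARs are identified from SAEs judged related and unexpected. If a site relies on the exemption and files no SAE, the article describes no other step by which the event enters that assessment. The exemption applies before causality is considered, although the same section requires causality and expectedness to be assessed.

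7. **Is SAE reporting restored elsewhere?** No. The visit schedule, outcome definitions, DMC and expert panel all capture or review lesion worsening, but none is described as 24-hour or expedited reporting.

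**The case against.** The strongest reply is that little is actually lost, and much of it stands.

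- **A SUSAR is not ruled out.** A reader might infer that an exempt event can never become one. The text does not support this. It waives a duty to report; it neither forbids reporting nor says that the event is not an SAE. The SUSAR sentence does not confine itself to SAEs that were reported.
- **SARs have their own 24-hour route.** On the plain wording a suspected serious reaction should still be sent in. This narrows the problem to an unresolved conflict between two rules, but the conflict remains.
- **Harm is still captured.** Lesion worsening is recorded as adverse events and through the outcomes on healing, paradoxical reaction, secondary infection and recurrence. The DMC sees safety and efficacy data, not SAE listings alone. The inference that an imbalance in lesion worsening would be hidden from the DMC is therefore not supported.
- **The hypertension text is a precaution.** A reader might take it as a statement that trial treatment will affect blood pressure. It says only that monitoring will be close and that adjustment is possible.
- **The term could mean medical history other than the study disease.** That reading is possible, but the article does not state it, and it would still leave serious worsening of comorbidities exempt.
- **The article condenses a full protocol.** That would answer a missing detail. Here the article states a rule without qualification, and the rule itself is too wide.

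The trial's general commitment to GCP and to regulatory guidelines does not tell a site which of the conflicting sentences to follow.

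**Conclusion.** The concern holds in limited form. The exemption is badly drawn: it allows serious, unplanned worsening of a pre-existing condition to go unreported as an SAE, and on the plain wording that includes the Buruli lesion. It also conflicts with the SAR and SUSAR rules of the same section. What is at risk is consistent SAE and expedited reporting across the three sites, and the SAE comparison between arms. Other capture of harm remains in place, and no primary or secondary efficacy estimate depends on this sentence.

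The number of affected events cannot be derived, because the article gives no rate for serious lesion or comorbidity events. Any count would rest on an unanchored assumption, and the conclusion does not need one. It does rest on reading the lesion as a pre-existing condition, which follows from the entry criteria and the absence of a definition. For comorbidities it holds without that reading. The point deserves correction because it concerns expedited safety reporting and is cheap to repair.

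**What to change.** Amend the sentence in the Harms section in three respects:

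1. Limit the exemption to planned hospitalisation for elective treatment of a pre-existing condition that has not worsened since baseline.
2. State that worsening of a pre-existing condition, including the Buruli lesion, that meets a seriousness criterion is reported as an SAE and assessed for causality and expectedness.
3. Reconcile the sentence with the 24-hour SAR duty and the SUSAR rule, so that a site can see which one governs.

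The change concerns reporting only and leaves treatment and visits as they are. Recruitment began in November 2021, so the amendment must go through the steering committee, sponsor, ethics committees and regulator as the article provides. The practical cost is site retraining and a few more SAE forms.

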### Ethics

The clinical trial will be carried out in line with the principles of the Declaration of Helsinki and as per the Guidelines of the Food and Drugs Authority (FDA), Ghana using the 2016 ICH E6 R2 Guidelines. Appropriate insurance is in place to cover any harms occurring as a result of trial participation. The trial will ensure all participants are additionally covered by Ghana Health System national insurance policy.

#### Consent or assent

A trained researcher in Good Clinical Practice (GCP) will screen all individuals for eligibility. Eligible individuals will be provided with a Participant Information Leaflet and verbal information as necessary about the study by a research fellow in English or in another language (*e.g.* Twi) if preferred by the participant. Written informed consent will be obtained from the potential study participant. For potential study participants under 18 years of age, consent from a responsible adult (parent, relative, guardian, legal representative) will be obtained. Assent shall be obtained from study participants between 12 and 17 years. This will be uploaded into the REDCap database.

#### Research ethics approval

This study has been approved by the Food and Drugs Authority (FDA) - Ghana (reference number, FDA/CT/2110), the Ghana Health Service (reference number, GHS-ERC 003/01/21), the London School of Health and Tropical Medicine; LSHTM (reference number, 22912) and the KNUST; School of Medical Sciences, Committee on Health Research, Publication and Ethics (reference number CHRPE/AP/030/21). The study has also been registered on the Pan African Clinical Trials Repository with the reference number; PACTR202011867644311. Should there be any changes in the approved documents, the aforementioned authorities will be consulted.

#### Plans for communicating important protocol amendments to relevant parties (e.g. trial participants, ethical committees)

Any protocol amendment will be reported to the Trial Steering Committee for approval. The Sponsor, London School of Hygiene & Tropical Medicine, relevant ethics committees and regulatory authority (see research ethics approval) will subsequently be notified.

#### Access to data

Data will be available upon request to the appropriate authorities and data management teams included in the study.

#### Dissemination policy

Results will be provided to the Ethics Committee and the Regulatory bodies. Results will additionally be disseminated by publication in open access peer-reviewed journals and presented at the annual WHO meetings on BU. For journal publications, authors will be included in line with an overarching publication policy covering the SHARP project and the recommendations of the International Committee of Medical Journal Editors (ICJME).

## Discussion

Neglected tropical diseases, including BU, continue to pose challenges to public health especially in low-and middle-income countries. The WHO continues to advocate for improved diagnosis and management to reduce disabilities associated with NTDs^38^. While there has been significant progress in the management of BU disease, the median time to wound-healing is still long, with the possibility of affected individuals suffering multiple complications including long term disability as well as a substantial economic burden. In this regard, interventions that reduce healing time and improve treatment outcomes will be a step in the right direction.

Beyond their clinical benefits, such interventions have the potential to create substantial financial and economic savings. Previous studies have shown that the longer healing/treatment time result in higher costs for patients and their caregivers and families. While the cost of antimicrobial treatment is free in BU endemic countries, individuals may incur significant costs related to transportation, subsistence, wound dressings, admission fees, and adjunctive surgery like wound debridement or skin grafting. Further, there might be indirect costs emanating from loss of productive work hours for affected persons and their caregivers. BU patients and caregivers also face significant mental health burden and a reduced quality of life^4,39,40^.

This trial sets out to test the efficacy of an innovative intervention, HR, that has the potential to shorten time to healing and reduce paradoxical reactions and secondary infections. The trial has several strengths: this is the first randomised controlled trial of HR for BU treatment and includes what is expected to be the first cost effectiveness analysis of BU, which is important for ensuring that the limited resources available are used as efficiently as possible to improve outcomes for affected individuals. It is recognised that participants may experience recall bias of the costs of BU prior to the study; however, the cost and health-related quality of life estimates from this trial will add to the limited evidence on this aspect of BU. It is expected that the intervention will improve the clinical outcome of BU-affected individuals while reducing the economic consequences of suffering the condition. The intervention aligns with the objectives of the WHO roadmap for NTDs and has the potential to change WHO recommendations for the treatment of BU in endemic countries.

## Figures and Tables

**Table 1 T1:** Schedule of procedures for study participants. BU: Buruli ulcer.

Activity	Screening	Week 0	Week 2	Week 4	Week 6	Week 8	Monthly	12 Months	Treatment failure
Written informed consent	X								
Inclusion and exclusion criteria and socio-demographics	X	X							
Randomisation		X							
History and physical exams		X	X	X	X	X	X	X	X
Clinical assessment	X	X	X	X	X	X	X	X	X
Adverse events			X	X	X	X	X	X	X
Clinical assessment of the patient and lesion		X	X	X	X	X	X	X	X
Measurement of lesion size		X	X	X	X	X	X	X	X
Photograph of lesion by digital camera	X	X	X	X	X	X	X	X	X
Counselling and testing for pregnancy	X			X		X			
Swab/FNA for PCR	X	X							X
Swab/FNA for 16S rRNA (0, 2, 4, 6, 8 weeks and then monthly if not healed)		X	X	X	X	X	X		X
VAS		X	X	X	X	X	X	X	X
Functional limitations assessment		X	X	X	X	X	X	X	X
Health-related quality of life (QALY, DALY) for economic evaluation		X	X	X	X	X	X	X	X
Household costs of BU and of care seeking		X	X	X	X	X	X	X	
Socioeconomic status		X	X	X					

## Data Availability

**No data are associated with this article.** Zenodo: Additional files for BuruliRifDACC, https://doi.org/10.5281/zenodo.7263508^28^ This project contains the following extended data: BuruliRifDACC_ICF.pdf Zenodo: SPIRT checklist for “Buruli-RifDACC: Evaluation of the efficacy and cost-effectiveness of high-dose versus standard-dose rifampicin on outcomes in *Mycobacterium ulcerans* disease, a protocol for a randomised controlled trial in Ghana”, https://doi.org/10.5281/zenodo.7263508^28^
